#### 2.2.2. Inclusion and Exclusion Criteria

Inclusion criteria:Age ≥ 18 years old;Ischemic or hemorrhagic acute stroke;Inclusion > 3 and ≤ 12 months post-stroke,Rankin score ≥ 3 and ≤ 4 at inclusion,Written informed consent,Affiliation to social security,Hip minimal abduction of 25 degrees bilateral with no history of hip dislocation and/or dysplasia,Certificate of non-contraindication.

Exclusion criteria:Major cognitive impairment affecting comprehension (Mini Mental State Examination test < 24 points);Global or sensory aphasia;Neurological or psychiatric co-morbidity (other than mild to moderate post-stroke depression);Evidence of uncontrolled seizures;Substance abuse;History of uncontrolled pain;History of allergic reactions to dust and/or horsehair, or severe asthma;Body weight ≥ 110 kg;Contraindications to physical activity;Inability or medical contraindication to travel to the Institute Equiphoria;History of therapeutic horse riding or hippotherapy during the last 6 months;Pregnant or lactating women;Patients participating in other biomedical research or in a period of exclusion.

### 2.3. Interventional Methods

#### 2.3.1. Treated Group

The hippotherapy exercises will consist of four phases performed sequentially:On the horse simulator (Racewood Ltd., Tarporley, UK): (i) 10 min of warm-up allowing patient’s familiarization, muscles’ warm-up, and nervous system facilitation (the Therapeutic Equine Simulator System TESS© has been used as valuable complement for hippotherapy in postural balance rehabilitation [12]); in some cases, the simulator can be used for the entire 1 h session depending on the patient’s needs;On the horse: (ii) 5 min passive and active mobilization of the lower limbs, passive and active stretching of the different muscle groups; (iii) 40 min work on global postural balance and fine-tuning of postural responses (eyes open and closed), work on upper limbs’ fine motor skills by manipulating objects, strengthening of different muscle groups, reinforcement of the body schema and body image [49], breathing techniques and visualizations; and (iv) 5 min relaxation with passive mobilizations and passive stretching, especially of the flexor muscles.

The hippotherapy protocol is substantially the same for every patient knowing that a reinforcement of postural balance, symmetry, hip and shoulder dissociation, spinal joint mobility, and muscle tone regularization are needed in both Rankin 3 and 4 patients. These will be obtained through the horse movement at a walk and the simulator movement. During hippotherapy, the postural balance work and the muscle tone regularization are background tasks [11,12]. The physiotherapist will simultaneously work the upper limb through repetitive task-specific training, muscle strength training, bilateral training, and mental practice. The intensity of the exercises will be fully tailored and will depend on the patient’s clinical heterogeneity, fatigability, and confounding factors.

Standing and walking is not mandatory for mounting a horse during hippotherapy. The institute is equipped with a ramp, which allows for the wheelchair to be positioned alongside the horse. Our trained staff operate the transfers of non-walking patients. Once on the horse, the patient is usually able to maintain an adequate postural balance. The therapist walking alongside the horse during the session is an occasional form of support when needed. The horse is equipped with a specially manufactured leather pad with handles (no saddle, no stirrups), allowing for the patient’s maximum freedom of movement and contact with the horse’s back.

During the remaining 18 weeks, the treatment options for each patient will include physiotherapy (motor training and functional training), occupational therapy, language therapy, and psychological and social support in the CHSF (see Section 2.3.2 below).

#### 2.3.2. Control Group

Patients of the control group will follow a standard outpatient rehabilitation treatment during 22 weeks, consisting of a combination of five half-day physiotherapy, occupational therapy, speech therapy and psychotherapy sessions per week according to the patient’s needs. For the patients with a modified ranking scale comprised between 3 and 4, it is likely that the work targeted on gait, balance, and mobility will focus on gait-oriented physical fitness training, repetitive task training, muscle strength training, and the treadmill training when possible. People with difficulty using their upper limb should be given the opportunity to undertake as much tailored practice of upper limb activity as possible. Interventions, which can be used routinely, involve constraint-induced movement therapy in selected people, repetitive task-specific training, and mechanical-assisted training. One or more of the following interventions can be used in addition to the ones above: mental practice, electrical stimulation, biofeedback in conjunction with conventional therapy, bilateral training, and mirror therapy. Moreover, special attention will be paid to manage mild to moderate spasticity through early comprehensive rehabilitation. Additionally, contractures must be carefully monitored and prevented by conventional motion therapy. Particularly common is the loss of shoulder external rotation, elbow extension, forearm supination, wrist and finger extensions, ankle dorsiflexion, and hip internal rotation. People with severe weakness tend to develop contractures. Any joint or muscle not regularly used can be subject to soft tissue complications, which will eventually limit movement and may cause pain.

As several techniques are likely to be used, a record of the number of rehabilitation sessions (physiotherapy, occupational therapy, speech therapy, and psychotherapy) and their type will be collected for each patient during the study period and used as a covariate.

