Existing standard procedures are not fully suitable for studying complex interventions, such as neurorehabilitation, in a clinical trial. Indeed, this comprehensive approach must be conducted according to specific ethical considerations and it is therefore inappropriate to suspend and/or delay a validated therapy and replace it with an experimental procedure alone, or to provide a true “placebo procedure” in a control group. Therefore, the study will have the following two arms: (i) a treatment arm where patients will receive 4 weeks of hippotherapy care combined with 18 weeks of conventional neurorehabilitation; and (ii) a control arm where patients will receive 22 weeks of conventional neurorehabilitation alone. The primary aim of this clinical trial is to compare the effect of neurorehabilitation through hippotherapy versus conventional care alone on the functional independence of patients in the first year post-stroke. The secondary endpoints will broaden the global evaluation of the patient outcomes and measure the impact of the program on the quality of life and burden of their close caregivers.

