## 2. Materials and Methods

### 2.1. Design

We will conduct a randomized open, prospective two-arm controlled trial with blinded clinical evaluations on the effectiveness of hippotherapy (plus conventional neurorehabilitation) versus conventional neurorehabilitation alone. Due to the nature of the clinical trial, participants will know which treatment they will receive and investigators may also be aware of the treatment modality during the patient inclusion/randomization process. In this context, a double- or single-blind procedure is not entirely appropriate/possible. In order to mitigate the effect of factors that are not related to the treatment or intervention being tested, the patient’s functional abilities and emotional sphere will be assessed by two external actors, i.e., two physiatrists associated with the Centre Hospitalier Sud Francilien (see below). These physicians will conducted blinded face-to-face clinical assessments (they have no link with the investigation staff; they do not have access to the whole eCRF; they will also be blinded to previous assessments; and patients and their caregivers will be carefully advised not to disclose the treatment modality they are following). The study will occur at the Equiphoria Institute (La Canourgue, France: https://www.equiphoria.com/en/; accessed on 8 September 2021) for the hippotherapy program and at the Neurology Service of the Centre Hospitalier Sud Francilien (CHSF Corbeil-Essonnes; https://www.chsf.fr/nos-service/medecine/neurologie/; accessed on 8 September 2021) for the conventional neurorehabilitation. Randomization will be stratified by age (18–59 years, 60–74 years, and ≥75 years), stroke type (ischemic versus hemorrhagic), and degree of disability (Rankin scores 3 or 4) to ensure the groups’ homogeneity. The randomization and anonymization of the patient will be performed automatically by an algorithm in the eCRF following the completion of the patient’s initial data at inclusion. The clinical tests will be stored (eCRF) in a secure digital platform of the external subcontractor (CRO) for delayed treatment.

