#### 2.1.1. The Study’s Protocol

The protocol’s shape relies on our own clinical experience over the last decade [6,7,8,9,10,11,12,13,35]. The hippotherapy approach will comprise three cycles. The first one consists of two-week daily sessions. This first phase aims to (i) evaluate the patient’s neuro-functional capacities, and (ii) build the initial treatment taking into account the silent barriers that may exist (e.g., PTSD, fatigue, pain, and fear) and that strongly interfere with the individual’s functional outcome [36] developing ways to overcome them. After a nine-week “hippotherapy wash out” period during which the patient continues with the conventional neurorehabilitation care, an intermediate one-week daily hippotherapy cycle followed. Then, after a second nine-week “hippotherapy wash out” period, a final one-week daily hippotherapy cycle will occur. The conventional outpatient rehabilitation for each patient in the hippotherapy group will be temporarily suspended during the hippotherapy cycles. Six months after the end of the rehabilitation protocol, patients will be monitored for sustainability of functional gains. The entire protocol will last 48 weeks (see Figure 1).

The so-called “hippotherapy wash out” period has three main objectives: fixing of the new schemes; translating them to day-to-day skills; and revealing new unmet needs. Our current clinical practice supports the proposed rhythm for rehabilitation through hippotherapy (see Section 2.3.3).

A battery of validated tests are used to study the patient’s level of disability, sensorimotor function, and quality of life. A measurement of the quality of life and burden of caregivers is also included. Patients will undergo evaluations prior and at the end of the neurorehabilitation program, as well as six months after the end of the neurorehabilitation program (end of the study).

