#### 2.1.4. Sample Size and Recruitment

From the related data [47], the sample-size calculation was based on a minimum reasonably significant difference in the primary outcome (Functional Independence Measure) of 22 points with a standard deviation of σ = 28.43 [48]. To detect that difference with a power of 80% using a two-sample *t*-test at a two-sided significance level of 5%, a total of 44 patients in the randomized arms (22 per arm) will be required. We will recruit 52 patients into the study, to allow for an attrition rate of around 20%.

Recruitment will be conducted during a 12-month period. The study will end when the last patient enrolled undergoes a neurological evaluation to determine the durability of functional recovery.

The end-of-treatment assessment will be completed within two weeks of the end of 22 weeks of treatment and the end-of-protocol assessment will be completed 26 weeks after the end of treatment. The protocol began in the fourth quarter of 2021 and will run through the third quarter of 2024.

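### Rehabilitation session counts, recorded after randomisation and lower by design in the hippotherapy arm, should not be a covariate in the main between-arm models

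*Protocol article*

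**What the plan says.** Section 2.3.2 (Control Group) provides for counting each patient's sessions of four conventional therapies, by number and by type. It states that these data "will be collected for each patient during the study period and used as a covariate". It does not name the analysis that will use the covariate. Hippotherapy is not among the therapies counted.

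Four other statements bear on this:

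- Randomisation (Section 2.1) is done by the eCRF "following the completion of the patient’s initial data at inclusion", before any of these sessions is counted.
- The treatment arm (Section 1) receives "4 weeks of hippotherapy care combined with 18 weeks of conventional neurorehabilitation", against 22 weeks of conventional care in the control arm.
- The gap is built in: conventional care in the hippotherapy group "will be temporarily suspended during the hippotherapy cycles" (Section 2.1.1).
- Control care (Section 2.3.2) is described as "consisting of a combination of five half-day physiotherapy, occupational therapy, speech therapy and psychotherapy sessions per week according to the patient’s needs". Section 2.3.1 refers to the same section for the hippotherapy arm's remaining 18 weeks.

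Section 2.4.2 tests differences between and within groups by multilevel analysis, names Friedman's test for the primary and secondary outcomes, and allows post hoc correlation and covariance procedures. The covariates it mentions are background variables found to be unbalanced at baseline; it does not mention session counts.

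**The concern.** The trial randomises between two strategies, and giving up four weeks of conventional care is part of one of them. A model that holds the number of conventional sessions equal removes that part of the strategy. It asks what hippotherapy adds at the same conventional dose, a question that randomisation does not protect.

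Because sessions follow need, the count may also reflect how the patient is recovering, which treatment can itself affect. The count therefore partly stands in for the arm and partly for the patient's course.

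At stake are the meaning of the between-arm estimate for FIM and the secondary endpoints, and usually its precision. The sentence in Section 2.3.2 is a positive commitment to an analysis, so this is not a detail merely left to the analysis plan.

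**Working it through.** **Inputs from the protocol.** The FIM difference and SD are "of 22 points with a standard deviation of σ = 28.43" (Section 2.1.4), with 22 per arm and a two-sided 5% test. Planned conventional half-days are 22 × 5 = 110 (control) and 18 × 5 = 90 (hippotherapy, same weekly rate). The gap is D = 20, which is 20/110 = 18%.

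**Assumed, because the protocol gives neither.** The within-arm SD of session counts, s, and the within-arm correlation of sessions with FIM, r. One counted session per half-day is also assumed.

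**The plan's own figure.** The unadjusted standard error is 28.43 × √(2/22) = 8.57. The two-sample t-test at 22 per arm then has 71% power (73% by the normal approximation), not the stated 80%; a two-sided test needs 28 per arm by the t-test. That is a separate matter. Here 71% serves only as the unadjusted baseline.

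**Shift of the estimate.** With linear adjustment,

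adjusted effect = (difference in mean FIM) − b × (90 − 110) = (difference in mean FIM) + 20b,

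where b is the within-arm FIM slope per session, b = r × 28.43/s.

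- s = 10, r = ±0.3: b = ±0.853, shift ±17.1 points.
- s = 20, r = ±0.3: b = ±0.426, shift ±8.5 points.
- s = 30, r = ±0.3: b = ±0.284, shift ±5.7 points.
- A much weaker slope of ±0.1 to ±0.2 points per session shifts the estimate by ±2 to ±4 points.

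Simulation (10,000 trials per setting, 22 per arm, true effect 22) agrees. The unadjusted mean stayed at about 22.0. The adjusted mean was 39.2 (s = 10, r = +0.3), 4.9 (s = 10, r = −0.3), 30.4 (s = 20, r = +0.3) and 13.5 (s = 20, r = −0.3).

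**Precision.** Variance inflation from collinearity with arm is VIF = 1 + D²/(4s²). The net variance ratio is VIF × (1 − r²). Adjustment gains precision only if |r| exceeds √(1 − 1/VIF). Power is for an effect of 22 with r = 0 (t-test).

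| s | VIF | SE at r = 0 | Power at r = 0 | Break-even \|r\| |
|---|---|---|---|---|
| unadjusted | – | 8.57 | 71% | – |
| 5 | 5.0 | 19.17 | 20% | 0.89 |
| 10 | 2.0 | 12.12 | 43% | 0.71 |
| 20 | 1.25 | 9.58 | 61% | 0.45 |
| 30 | 1.11 | 9.04 | 66% | 0.32 |

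The loss can be offset. At s = 20 and r = 0.5 the variance ratio is 1.25 × 0.75 = 0.94, but the shift is then 0.5 × 28.43/20 × 20 = 14.2 points.

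**The case against.** The strongest reply is that Friedman's test, named for FIM and the secondary outcomes, takes no covariate, and that Section 2.4.2 does not list session counts among its covariates. The count might be meant only for the post hoc covariance work, which is close to an acceptable exploratory use. This stands in part. A reader might infer that the primary result is certain to be biased, and the protocol does not show that. But Section 2.4.2 also tests between-group differences by multilevel analysis for primary and secondary endpoints, and Section 2.3.2 does not confine the covariate to exploratory work.

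A reader might also infer that adjustment would favour hippotherapy by crediting it for displaced sessions. That needs more sessions to go with better FIM. Sessions are given according to need, so sicker patients may receive more, and the shift would then go the other way.

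Nor is lost precision a certainty. It depends on s and r, and the table's power figures hold the effect at 22 while adjustment also moves the estimate. If the shift were +2 to +4 points, the chance of a significant result would be about 49–55% at s = 10 and 69–76% at s = 20. That, however, is power for a different contrast.

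Finally, 90 versus 110 counts one session per half-day, although several could fall in one. The study period might also run to week 48, which could widen the spread. These points change D and s, and hence the size. They do not change the fact that the count comes after randomisation and differs by design.

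**Conclusion.** The point holds in a limited form. Any between-arm model that follows Section 2.3.2 as written would condition on a variable that arises after randomisation and that the design makes unequal. It would not estimate the contrast of 4 weeks of hippotherapy plus 18 weeks of conventional care against 22 weeks of conventional care.

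That conclusion needs no assumed figures. The size does. The shift is about 20 times the within-arm slope, of unknown sign, and is zero only if sessions and FIM are unrelated within arms. In that case, for s between 5 and 20, variance is still inflated 5.0 to 1.25 times and power is about 20% to 61% instead of 71%. These figures assume linear adjustment and one counted session per half-day. The named Friedman tests are not affected.

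**What to change.** In Section 2.3.2, and in the analysis plan if it repeats the commitment, replace the covariate clause with wording such as: *The number and type of rehabilitation sessions will be reported descriptively by arm as treatment received. They will not enter the main between-arm models for the primary or secondary endpoints. Covariates in those models will be restricted to variables measured before randomisation. Any session-adjusted or dose-response analysis will be labelled exploratory.*

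The cost is a short text change, best made before the data are analysed. The session records are still collected, and neither care, assessments nor sample size changes.

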#### 2.3.3. Intensity and Effectiveness

It is difficult to determine the minimum effective quantity of the required neurological rehabilitation. Scientific evidence is lacking and studies have biases of several kinds. To date, the effectiveness of many rehabilitation techniques has not been systematically demonstrated. According to a 2014 review of the literature [50], the studies carried out are highly heterogeneous (e.g., type of rehabilitation, included patients, quality of structures, and type of evaluation) and have a low methodological quality [50,51,52]. The overall effectiveness of stroke rehabilitation has been substantiated from older studies generally mainly showing reductions in mortality, dependency rates, and risk of institutionalization.

On the one hand, in this rather empirical context, sessions of at least 45 min by type of rehabilitation are commonly recommended (more if the patient can bear it). It is accepted that the frequency is daily or at least 5 days a week. Rehabilitation should be conducted for at least 8 weeks “as long as improvement continues”. During the first two weeks, frequent, short sessions of progressive intensity are preferred. The intensity with which rehabilitation is conducted varies depending on dispensing structures. Thus, rehabilitation in a specialized service with full hospitalization or day hospitalization offers possibilities to perform intensive multiple rehabilitation, which is more difficult to perform with independent professionals [50].

On the other hand, a hippotherapy session lasts one hour per day during which between 3000 and 4500 contractions of each postural muscle are sequentially realized in a background mode (horse at a walk) in parallel to other requests (fine motor skills, cognitive elaboration, and psychic work), well beyond what a conventional rehabilitation session allows. Given the intensity of each session that mobilizes the individual in his/her entirety (e.g., somatic, sensory, cognitive, emotional and motivational, and psychic spheres), and relying on our clinical experience over the last decade, we unequivocally respect a certain rhythm by integrating the duration of the patient’s processing of physical/mental skills and the ensuing fatigue. Additionally, thanks to the enriched environment brought by hippotherapy, we notice continuous functional improvements, even beyond the theoretical period of consolidation of the neurological outcome after injury [53,54]. Overall, the strong stimulation of the sensory, sensitive, and motor spheres promotes and interacts with the mechanisms related to the tasks’ performances in the cognitive and emotional domains through the activation of multiple neural networks [35,55]. The degree of change associated with neuroplasticity through hippotherapy is most likely linked to both the relevance of the activity and the intensity and frequency of the elements that constitute it [56,57,58]. A systematic validation is carried out at the Equiphoria Institute to provide a solid theoretical foundation for this approach.

#### 2.3.4. Safety/Adverse Events

At each evaluation, the investigator will determine whether any adverse events or serious adverse events (AEs or SAEs) occurred. All adverse events occurring during the study will be recorded on the appropriate case report form (eCRF) page by the investigator. The nature, severity, and relation of the adverse event to the study protocol and treatment will be documented. A safety plan has been duly integrated in the Trial Master File.

### 2.4. Data Collection and Analysis

The data will be duly anonymized and blindly manipulated in the eCRF. Data management will be performed by a CRO already contracted according to a data management plan. A data monitoring committee composed by the CRA of the CRO and the principal investigators of the CHSF will oversee the follow-up of the data collection accuracy and reporting of adverse events.

